**Figure 3 f3:**
[figure not shown]
Harmful substance use induces activation of glia cells and neuroinflammation.

Consistent with this, prior work supports the relationship between SUDs and peripheral markers of pro-inflammatory biological processes. For example, individuals with AUD exhibit an activation pattern characteristic of a pro-inflammatory response that persists even after alcohol withdrawal (131–133). Cocaine abstinence was also associated with higher levels of pro-inflammatory cytokines (IL-2, IL-6, and IL-17) in a sex-specific manner (134). Importantly, higher IL-6 levels have been correlated with worse EF performance (135). In individuals with opioid use disorder, higher levels of pro-inflammatory cytokines (IL-1β, IL-6) were associated with worse episodic memory performance and worse treatment response to methadone (136, 137). A similar pattern of increased pro-inflammatory activation is also observed in patients with cannabis use disorder (138).

Inflammasome activation is frequently reported in different neuropsychiatric conditions (139–141), where it co-occurs with cognitive dysfunction (142–148). However, the relationship between inflammasome activation and cognitive impairment among adults with SUDs remains understudied. The overarching goals of P3 are to investigate pro-inflammatory changes and inflammasome activation as a mechanism associated with executive dysfunction in SUDs.

### Objectives

The primary objective of P3 is to investigate the impact of inflammasome activation on EF domains in SUDs. Its secondary objective is to investigate the impact of inflammasome activation on structural and functional brain parameters in SUDs (integration with P2).

#### H1

Higher inflammasome activation (i.e., high expression of NALP3) will be associated with: (a) worse inhibition (b) lower working memory updating, and (c) reduced set shifting ability.

#### H2

Higher inflammasome activation will be associated with: (a) lower gray matter in the prefrontal cortex; (b) reduced activation of the default brain network; (c) less connectivity in neural circuits underlying EFs.

### Methods and planned analyses

#### Blood collection, sample preparation, and storage

P3 draws on the same participant pool recruited for P1. Blood is collected into two EDTA (8 cc) and one citrate (4.5 cc) tubes. After processing, the plasma and buffy coat aliquots are immediately stored at -80°C until analysis. Blood samples and extracted DNA are banked for potential future integrative analyses (see Project 7).

#### Laboratory analysis for plasma biomarkers

We will measure the phosphorylated and non-phosphorylated proteins isoform levels of the NALP3 complex using Western Blot. The ratio between non-phosphorylated and phosphorylated isoforms of NALP3 will be used as a proxy measure of the activation of the inflammasome pathway. Additionally, we will measure the plasma levels of the pro-inflammatory cytokines IL-1β, IL-18, and proCaspase-1 using a multiplex immunoassay (bead-based multiparametric assay).

The immunoassays will be analyzed using the Luminex xMAP technology^®^ (Luminex 200). The assay has very low cross-reactivity, and this technology has a higher sensitivity to detect very low concentrations of different analytes. The intra- and inter-assay coefficient of variance for the assay is below 10% for most of the analytes measured.

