#### Proposed analysis

To test the association of the biomarkers with the three EF domains and neuroimaging outcomes, we will use Pearson correlation and linear multiple regression models. The linear models can be expanded to include potential covariates, if necessary. The total sample size of 400 subjects will be sufficiently powered to detect small effect sizes of correlation coefficients of 0.11 (α=0.05, statistical power of 80%) to 0.14 (α=0.05, statistical power of 95%).

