Blood samples will be drawn weekly and 24 hours after discontinuation of the liquid diet (**Figure 4**) to verify 1) blood alcohol levels (BALs) exceeding 100mg% during exposure and 2) the absence of alcohol 24 hours after cessation when behavioral testing begins. BALs will be assessed using an ANALOX machine. Serum samples will also be utilized for measuring peripheral inflammasome biomarkers. Inflammasome activity will be determined by the phosphorylated/non-phosphorylated NALP3 ratio in peripheral blood mononuclear cells, along with investigating inflammatory markers (NF-KB, ERK, p38MAPK) and cytokines (IL-1β, IL-18, Caspase-1). Luminex xMAP technology^®^ will be employed for biomarker analyses.

After behavioral assessments, rats will be euthanized, and brains dissected for immunofluorescence staining and molecular analyses on regions of interest (prefrontal cortex, VTA, nucleus accumbens and hippocampus). Rostro-caudal coronal sections will be stored at -20°C for neuroinflammation, noradrenergic, and GABAergic marker analysis. RNA and proteins will be extracted from homogenized tissue, allowing for cDNA conversion, quantitative PCR, and Western Blot analyses. The markers examined include, but are not limited to, SST, PV, α5-GABRA, α1 GABRA, BDNF, and other GABAergic markers. Similarly, qPCR, immunostaining, and Western Blot analyses against sterile inflammation biomarkers (NALP3, NF-KB, ERK, p38MAPK, IL-1β, IL-18, Caspase-1) will validate the correlation of peripheral and central biomarkers in a region-specific manner. Investigation of changes in noradrenergic system markers (NET, α1 receptor, α2 receptor) will complement NM-MRI work outlined in P2.

The blood and brain samples collected will form a repository for subsequent biomarker analyses related to executive dysfunction in AUD. As Objective 3 establishes this repository, the analysis of these samples (peripheral or central) will be influenced by findings from other projects. Consequently, additional exploratory investigations of biomarkers will be conducted in these samples when other projects identify relevant pathways or markers in the clinical population.

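### Project 3 and Project 5 index inflammasome activation by NALP3 ratios written in reciprocal order, and Project 3's H1 describes it as expression; the direction meaning more activation is never stated

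*Protocol article*

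**What the plan says.** The primary objective of Project 3 makes inflammasome activation the exposure of interest: "The primary objective of P3 is to investigate the impact of inflammasome activation on EF domains in SUDs". Two hypotheses follow, and both are directional. H1 opens: "Higher inflammasome activation (i.e., high expression of NALP3) will be associated with". It then lists poorer performance in each of the three executive-function domains. H2 begins: "Higher inflammasome activation will be associated with: (a) lower gray matter in the prefrontal cortex", and goes on to brain-network activation and connectivity.

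The measurement rule is in Project 3, under Laboratory analysis for plasma biomarkers: "The ratio between non-phosphorylated and phosphorylated isoforms of NALP3 will be used as a proxy measure". What it stands in for is inflammasome activation. Both isoforms are to be measured by Western blot. For the association tests, Proposed analysis states: "we will use Pearson correlation and linear multiple regression models". It does not mention the scale of the ratio.

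The rat study (Project 5, Measures) says: "Inflammasome activity will be determined by the phosphorylated/non-phosphorylated NALP3 ratio in peripheral blood mononuclear cells".

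The article ties the two projects together. Project 5's Background presents pharmacological blockade of the inflammasome as completing and extending Project 3's correlational results. Table 5 lists synergy between Project 5's inflammasome work and Project 3's biomarker studies.

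**The concern.** The two projects use the same protein, the same two isoforms and the same construct, but name the isoforms in opposite order. A high value in one project is a low value in the other, yet each is presented as an index of activation or activity. H1 adds a further description, high expression, which neither ratio measures.

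A directional hypothesis needs an exposure whose direction is settled before the data are seen. If it is not settled, a correlation of either sign between the index and executive function can be presented as agreeing with H1 by choosing the orientation afterwards. The same ambiguity reaches H2, and it affects the comparison between species, where a finding that points the same way in humans and rats could be reported as a discrepancy.

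**Working it through.** The plan gives no figure to reproduce here. The check is a comparison of definitions, with some simple algebra.

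**Inputs.** Let U be the amount of non-phosphorylated NALP3 and P the amount of phosphorylated NALP3.

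| Place | Index of activation, as written |
|---|---|
| Project 3, Laboratory analysis for plasma biomarkers | R3 = U/P |
| Project 5, Measures | R5 = P/U |
| Project 3, H1 | expression of NALP3, a level; on one natural reading T = U + P |

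**Step 1: the two ratios.** R5 = P/U = 1/R3, so log R5 = −log R3. Any subject or animal ranked highest on one is ranked lowest on the other.

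**Step 2: effect on a correlation.** For any outcome Y, corr(log R5, Y) = −corr(log R3, Y). On the log scale the size of the correlation and its two-sided p-value are unchanged, and only the sign flips. A rank correlation behaves in the same way. On an untransformed scale the inverse is a decreasing but non-linear function, so the sign would ordinarily flip and the size would also shift. The amount depends on the spread of the ratio, which the documents do not give.

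**Step 3: the ratio against the expression wording.** Multiply U and P by the same factor k. Then T becomes kT, while U/P and P/U do not change. A participant can therefore have high NALP3 expression with any value of either ratio. The wording in H1 does not tell the reader which way up the ratio should go.

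**Step 4: what follows for H1.** Let Y be executive-function performance, with higher meaning better. H1 predicts a negative correlation between activation and Y.

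- If a higher U/P truly means more activation, Project 3 scores activation in the right direction and Project 5 scores it in reverse.
- If a higher P/U truly means more activation, Project 5 is right and Project 3 scores its primary exposure in reverse. Data agreeing with H1 would then show a positive correlation and read as contradicting it.
- If expression is what is meant, neither ratio measures it directly.

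With the ratios taken in the order written, at least one project is reversed under either of the first two cases. The article does not say which case applies, and it gives no reason for the difference between the projects.

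**The case against.** The strongest reply is that Project 3 is self-contained. Its method section names an index, and read in the order written this gives a direction; a sentence about rats does not alter a human analysis. The wording in H1 is a parenthesis in a hypothesis, not a measurement rule. This is partly right. Read alone and in order, Project 3 does have a direction. But a ratio between two things is looser than Project 5's explicit slash. If the phrase is taken as unordered, Project 3 has no direction at all; if it is taken as ordered, it conflicts with Project 5. A clarification is needed on either reading.

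A second reply is that Project 3 and Project 5 data are never pooled. Project 5 has its own analyses of variance and correlations, and its hypotheses speak of changes in biomarkers and reduced signs of neuroinflammation without predicting a signed correlation with the ratio. Both projects also measure IL-1β, IL-18 and caspase-1 or its pro-form, which could help to show a reversed index. This stands: no computed result combines the two ratios. The exposure is in the interpretation of Project 3's directional tests and in the narrative comparison across species.

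Three stronger readings are tempting, and the documents do not support them.

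- A reader might infer that Project 7 receives NALP3 inputs of opposite sign. The note to Table 4 says that rodent measures are not used directly as features in the human models, so only Project 3's values can enter.
- A reader might infer that Project 3 will correlate the untransformed ratio, so that the size and significance of the result would also depend on the denominator. Proposed analysis is silent on scale. A transformation is commonly left to the analysis plan, and any figure for that effect would rest on an assumed spread.
- A reader might infer that the randomised trial is affected. None of the six hypotheses in Project 4 uses NALP3.

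**Conclusion.** The contradiction is real and lies in what the article states, not in detail it omits. Project 3 and Project 5 define the index of one construct by ratios that are reciprocals in the order written, H1 describes that construct as a level, and no section says which direction means more activation.

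The size is a full reversal of sign in one project relative to the other. On a log scale the strength of association and two-sided significance would be untouched. The conclusion assumes only that the isoforms are read in the order printed and that a higher index is read as higher activation. It needs no assumption about the distribution of the ratio. The documents do not show which orientation is correct, so they do not show which project is reversed. The effect is confined to the interpretation of Project 3's H1 and H2 and to the comparison of Project 3 with Project 5.

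**What to change.** Before the assays are analysed:

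1. State one numerator and one denominator for the NALP3 index, and say in words which direction means higher inflammasome activation. The choice belongs to the investigators and should be justified from the biology.
2. Use that definition in both the laboratory section of Project 3 and the Measures section of Project 5. If the projects must differ, give the reason and say how results will be put on a common direction for comparison.
3. Reword the parenthesis in Project 3's H1 so that it describes the index actually measured.

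Analysing the log of the ratio is an optional addition; it would ensure that inversion changes only the sign.

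The cost is a few sentences. Project 3 already plans to measure both isoforms, and Project 5's ratio needs both as well, so no new samples, assays or participants are required.

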#### Proposed analysis

To test the association of the biomarkers with the three EF domains and neuroimaging outcomes, we will use Pearson correlation and linear multiple regression models. The linear models can be expanded to include potential covariates, if necessary. The total sample size of 400 subjects will be sufficiently powered to detect small effect sizes of correlation coefficients of 0.11 (α=0.05, statistical power of 80%) to 0.14 (α=0.05, statistical power of 95%).

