#### Proposed analyses

Behavioral data will be examined to assess the impact of alcohol exposure on EFs, utilizing ANOVA (or relevant non-parametric alternatives) followed by Tukey’s *post hoc* comparisons for statistical significance. In the alcohol-exposed groups, it is possible to observe subgroups of animals with higher susceptibility to alcohol than the others, suggesting existence of high-responders and low-responders.

For data collected weekly, data will be analyzed with repeated measures to identify animals that are more than 50% of the time over the mean, and animals that are more than 50% of the time under the mean to segregate high-responders and low-responders respectively. If such separation does not exist consistently, then analyses will focus on overall alcohol effect. For the second objective involving drug interactions, separate 2-way ANOVA with diet and treatment as factors will be applied, followed by Dunnett’s *post-hoc* comparisons (198). In Objective #3, blood sample data will be analyzed using Student’s t-test (Objective #1) or 2-way ANOVA (Objective #2) with diet and treatment as factors, followed by Dunnett’s *post-hoc* test. Brain analyses with qPCR and Western Blot will use 2-way ANOVA with diet and treatment as factors, followed by Dunnett’s *post-hoc* comparisons. Pearson or Spearman analyses will evaluate correlations between executive dysfunction and peripheral/central biomarker levels, with p-values adjusted for multiple comparisons using the Bonferroni method due to the potential high number of pairwise analyses.

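### Project 3's stated detectable correlations (0.11 at 80% power, 0.14 at 95%) do not follow from N = 400 even for one unadjusted test, and its imaging associations rest on about 200 participants

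*Protocol article*

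**What the plan says.** The Proposed analysis section of Project 3 is one short paragraph. It names the tests: "To test the association of the biomarkers with the three EF domains and neuroimaging outcomes, we will use Pearson correlation" and linear multiple regression, with covariates added if needed. It then gives the only power statement in Project 3: "The total sample size of 400 subjects will be sufficiently powered to detect small effect sizes", namely "correlation coefficients of 0.11 (α=0.05, statistical power of 80" per cent) up to "0.14 (α=0.05, statistical power of 95" per cent). It does not say whether the tests are one- or two-sided.

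The Project 3 objectives make inflammasome activation against the EF domains primary and the brain parameters secondary. H1 begins "Higher inflammasome activation (i.e., high expression of NALP3) will be associated with: (a) worse inhibition" and goes on to updating and set shifting, so it is one marker against three domains.

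Project 2, under Participants, expects about half of the cohort (n = 200) to be eligible for MRI and to consent. Its own analysis section says that 200 participants give more than 80% power for a correlation of about 0.2.

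**The concern.** The two power statements in the article do not fit together. For a fixed level and power, the detectable correlation shrinks roughly with the square root of the sample size. If 200 participants detect about 0.2 with 80% power, 400 should detect about 0.2/√2 = 0.14. Project 3 prints 0.11 for that case and uses 0.14 for 95% power.

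The sentence is the whole sample-size justification for Project 3, so a reader will use it to interpret a null result. A true correlation of 0.11 would be missed about four times in ten, not two in ten. For imaging outcomes the sentence is further off, because only about half of the cohort contributes data.

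**Working it through.** **Inputs.** From Project 3, Proposed analysis: N = 400, α = 0.05, power 80% and 95%, printed r = 0.11 and 0.14. From Project 2, Participants: about 200 with MRI. Sidedness is not stated, so both versions are shown.

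**Formulas (Fisher's z).**
- Detectable r = tanh[(z_α + z_power) / √(N − 3)]
- Two-sided power at r ≈ Φ[atanh(r)·√(N − 3) − 1.960]
- Required N = [(z_α + z_power) / atanh(r)]² + 3

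Normal quantiles: 1.960 (two-sided 0.05), 1.645 (one-sided 0.05; also 95% power), 0.842 (80% power).

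**Check of the method on Project 2's figure.** With N = 200 and r = 0.2: atanh(0.2) = 0.2027; 0.2027 × √197 = 2.846; 2.846 − 1.960 = 0.886; power = 81%. This agrees with Project 2's statement of more than 80%.

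**Attempt to reproduce Project 3's figures, N = 400, √397 = 19.92.**
- Two-sided, 80%: (1.960 + 0.842)/19.92 = 0.1406, so r = 0.140. Printed: 0.11.
- Two-sided, 95%: (1.960 + 1.645)/19.92 = 0.1809, so r = 0.179. Printed: 0.14.
- One-sided, 80%: (1.645 + 0.842)/19.92 = 0.1248, so r = 0.124.
- One-sided, 95%: (1.645 + 1.645)/19.92 = 0.1651, so r = 0.164.

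Neither version gives 0.11 and 0.14. A noncentral-t calculation agrees with these values to within 0.002. The 0.14 printed for 95% power is the two-sided value for 80%.

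**Power actually available at the printed correlations, N = 400.**

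| r | Claimed | Two-sided | One-sided |
|---|---|---|---|
| 0.11 | 80% | 59.5% | 71.1% |
| 0.14 | 95% | 80.2% | 87.8% |

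Example: atanh(0.11) = 0.1104; 0.1104 × 19.92 = 2.201; 2.201 − 1.960 = 0.241; Φ = 0.595.

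**Sample size that the printed figures would need.** r = 0.11 at 80%: 647 two-sided, 510 one-sided. r = 0.14 at 95%: 658 two-sided, 548 one-sided.

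**Imaging outcomes, N = 200, √197 = 14.04, two-sided.**
- 80%: 2.802/14.04 = 0.1996, so r = 0.197.
- 95%: 3.605/14.04 = 0.2568, so r = 0.251.
- Power is 34% at r = 0.11 and 51% at r = 0.14.

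**If the three NALP3 tests are adjusted.** The first Holm step uses 0.05/3 = 0.0167 two-sided, quantile 2.394. At N = 400: (2.394 + 0.842)/19.92 gives r = 0.161 at 80%, and (2.394 + 1.645)/19.92 gives r = 0.200 at 95%.

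**The case against.** Three defences deserve an answer.

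*H1 is directional, so the calculation may be one-sided.* This narrows the gap but does not close it. At N = 400 the one-sided values are 0.124 and 0.164, still above 0.11 and 0.14.

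*Project 2 already gives a figure for n = 200.* It does, and that figure is right. But Project 3 does not refer to it. The only sample size in a paragraph that covers imaging outcomes is the full cohort of 400.

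*The corrected values are still small correlations.* This stands. The qualitative claim that 400 participants can detect small effects survives; the numbers attached to it do not.

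A reader might also infer a stronger charge: that Project 3 tests every marker against every domain and imaging outcome without adjustment, and is laxer than Project 5, which reports correlations "with p-values adjusted for multiple comparisons using the Bonferroni method due to the potential high number of pairwise analyses". The article does not support that.
- It states no multiplicity rule for Project 3. It does not say that p-values will be unadjusted, and such a rule commonly sits in an analysis plan, which is not shown here.
- Project 5 is a separate rat study with many central and peripheral markers across several brain regions, so its rule does not contradict Project 3.
- The primary family is already narrow. The laboratory section uses the NALP3 ratio as the activation proxy and brings in the other markers as additions ("we will measure the plasma levels of the pro-inflammatory cytokines IL-1β, IL-18, and proCaspase-1"). Three independent tests give a chance of at least one false positive of 1 − 0.95³ = 14.3%. All four markers by three domains give 1 − 0.95¹² = 46.0% if independent, and 26% to 42% under assumed correlations of 0.3 to 0.7 among markers and among EF scores. A false link is therefore possible, but the text does not make it likely. A family of 24 tests would require splitting EF into deficits and biases, which Project 3 does not mention.

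Nor does multiplicity explain the power error: the printed figures already fail for one test at 0.05. Adjustment would only widen the gap.

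**Conclusion.** The power sentence in Project 3 is wrong as printed. The detectable correlations are understated by about a fifth: 0.11 against 0.140 at 80% power, and 0.14 against 0.179 at 95%. As shared variance (r²), this is 1.2% against 2.0%, and 2.0% against 3.2%. For imaging, where no separate figure is given, the honest values are about 0.20 and 0.25.

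These results assume a Pearson correlation with approximately normal data, usable EF and biomarker data from all 400 participants, and the 200 MRI participants that Project 2 anticipates. Any missing samples would raise the detectable values further. The conclusion does not depend on sidedness or on any view about multiplicity. It does not show that the cohort is too small for the programme.

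**What to change.** In Project 3, Proposed analysis:

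1. Replace the printed figures with r of about 0.14 (80% power) and 0.18 (95% power) for biomarker-EF correlations at N = 400, and state that the test is two-sided at 0.05. If one-sided testing is intended, say so and quote 0.124 and 0.164.
2. Add a separate statement for biomarker-imaging correlations at about N = 200: r of about 0.20 (80%) and 0.25 (95%), two-sided.
3. If the primary family of NALP3 against the three EF domains is to be tested with an adjustment such as Holm, quote about 0.16 (80%) and 0.20 (95%) for its first step at N = 400.

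The cost is wording only. Recruitment, assays and analyses are unchanged; the stated sensitivity becomes slightly less favourable.

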### Methods and planned analyses

#### Participants

All participants included in the total sample are invited to participate in a 1.5-hour MRI protocol. P2-specific exclusion criteria include the presence of MRI-incompatible metal implants, history of stroke, and claustrophobia. We anticipate approximately 50% of the entire sample (n=200) will be eligible and consent to MRI. Eligible participants are invited for a longitudinal scan at one-year follow-up; we anticipate 25% (n=50) being available and consenting to the repeat scan to assess longitudinal stability of our main measures. Given the specific safety requirements of MRI, it is possible that the final P2 sample will not be fully representative of the P1 sample in terms of demographics and clinical characteristics. If this is the case, we will consider this important caveat in interpreting any results using joint P1-P2 and conduct sensitivity analyses where appropriate.

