##### Proposed analysis

At baseline, task-based brain activation and brain structure will be investigated in association with SUD symptom severity, functional ability and out-of-scanner EF performance as measured by P1. Multivariate approaches (e.g., Partial Least Squares regression) will be used to investigate relationships between brain structure, function, and performance across the three EF tasks by identifying latent variables (LV) that capture covariance between the set of predictors (microstructure, performance) and outcome variables (functional activation). Individual brain scores reflecting the degree to which participants expressed the LV activation pattern will be correlated with SUD severity, functional ability and out-of-scanner EF performance, at baseline and on follow-up, uncovering neural factors crucial for improved functional outcomes. Age, sex, and primary substance of concern will be used as covariates. We anticipate the EF-domain-specificity of the neuroimaging results will mirror patterns obtained using out-of-scanner EF measures in P1. Although it is challenging to provide a power estimate for studies involving complex multivariate analytic approaches in neuroimaging, our proposed sample size is consistent with recent empirically derived recommendations to enhance reproducibility in task-based fMRI research (123). These studies suggest that a sample size of n=120 is sufficient to obtain a test-retest voxel-wise correlation >0.80 across most paradigms. Thus, our proposed cross-sectional sample size of n=200, is in line with these recommendations. Further, based on standard power analysis tools, a sample size of 200 allows power of >0.80 to detect small effect sizes on the order of r=0.2 or Cohen’s d=0.2.

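### Project 3's detectable correlations for N=400 (0.11 at 80% power, 0.14 at 95% power) do not reproduce, and no N=400 figure can serve its imaging outcomes, for which about 200 participants are expected

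*Protocol article*

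**What the plan says.** Project 3, Proposed analysis, first names the analyses: "To test the association of the biomarkers with the three EF domains and neuroimaging outcomes, we will use Pearson correlation and linear multiple regression models". Two sentences later it gives its only power statement: "The total sample size of 400 subjects will be sufficiently powered to detect small effect sizes of correlation coefficients of 0.11" at alpha 0.05 and 80% power, continuing "to 0.14 (α=0.05, statistical power of 95" per cent. It does not say whether the test is one-sided or two-sided, and it gives no separate figure for the imaging outcomes.

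Project 3, Objectives, makes imaging the secondary aim: "Its secondary objective is to investigate the impact of inflammasome activation on structural and functional brain parameters in SUDs (integration with P2"). The scans come from Project 2, whose Participants section says: "We anticipate approximately 50% of the entire sample (n=200) will be eligible and consent to MRI". Project 2, Proposed analysis, gives its own sensitivity: "a sample size of 200 allows power of >0.80 to detect small effect sizes on the order of r=0.2".

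**The concern.** The Project 3 statement supplies every input except sidedness, so it can be checked directly. The first sign of trouble is that 0.14, printed as the 95% power value, is the usual two-sided 80% value for 400 subjects.

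What is at stake is how Project 3's results are read. The statement implies that a true correlation of 0.11 would be missed one time in five, and one of 0.14 one time in twenty. If the real chances are higher, a null result on the primary biomarker objective carries less information than a reader of the article would assume. For imaging, the article gives a Project 3 reader no figure based on the number of people expected to have scans.

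**Working it through.** **Inputs.** N=400, alpha=0.05, and the pairs r=0.11 with 80% power and r=0.14 with 95% power (Project 3, Proposed analysis). The number with MRI is about 200 (Project 2, Participants). Sidedness is not stated, so both versions are computed.

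**Formulas** (Fisher z test of a Pearson correlation):
- detectable r = tanh[(z_alpha + z_power)/√(N−3)]
- power = Φ[atanh(r)·√(N−3) − z_alpha], plus a negligible opposite tail when two-sided
- required N = [(z_alpha + z_power)/atanh(r)]² + 3, rounded up

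Here z_alpha is 1.960 two-sided and 1.645 one-sided, and z_power is 0.842 for 80% and 1.645 for 95%. √397 = 19.925 and √197 = 14.036.

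**Step 1: the plan's own figures at N=400.**
- Two-sided, 80%: tanh(2.802/19.925) = 0.140, stated 0.11.
- Two-sided, 95%: tanh(3.605/19.925) = 0.179, stated 0.14.
- One-sided, 80%: tanh(2.486/19.925) = 0.124.
- One-sided, 95%: tanh(3.290/19.925) = 0.164.

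**Step 2: actual power at N=400 for the stated correlations.** atanh(0.11)·19.925 = 2.201 and atanh(0.14)·19.925 = 2.808.

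| r | stated power | two-sided | one-sided |
|---|---|---|---|
| 0.11 | 80% | Φ(2.201−1.960) = 59.5% | Φ(2.201−1.645) = 71.1% |
| 0.14 | 95% | Φ(2.808−1.960) = 80.2% | Φ(2.808−1.645) = 87.8% |

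**Step 3: N that the stated pairs would need.** For r=0.11 at 80%: 647 two-sided, 510 one-sided. For r=0.14 at 95%: 658 two-sided, 548 one-sided.

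**Step 4: attempts to rescue the figures.**
- Rounding: taking the stated values at their favourable limits (0.115 and 0.145), one-sided power is still only 74.4% and 89.7%.
- Exact test: the noncentral t version gives 0.139 and 0.178 two-sided, and 0.124 and 0.163 one-sided.
- Multiple regression with one tested predictor and up to ten in the model gives 0.139 and 0.178. Testing several predictors jointly raises the values.
- Reading the effect as f, f² or R² does not give the 0.11/0.14 pair either.

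**Step 5: the imaging outcomes at n=200, two-sided.**
- Detectable r at 80%: tanh(2.802/14.036) = 0.197.
- Detectable r at 95%: tanh(3.605/14.036) = 0.251.
- Power is 34.1% for r=0.11 and 50.7% for r=0.14 (46.2% and 63.1% one-sided).
- Project 2's own figure reproduces: for r=0.2 at n=200, power is 81.2%.

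**The case against.** **Sidedness is unstated and Project 3's hypotheses are directional.** This is fair, and one-sided testing narrows the gap in detectable r to 0.014 (0.124 against 0.11) and 0.024 (0.164 against 0.14). It does not close it: power remains 71.1% and 87.8%.

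**The error changes nothing in the design.** This largely stands. The 400 is the programme-wide recruitment target (Project 1, Design and participants), and nothing shows that Project 3's calculation set it. Correlations of 0.14 to 0.18 are still small, so the qualitative claim of power for small effects survives. The printed numbers do not.

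**The imaging sample size is already disclosed in Project 2.** True, and the power statement names the total sample of 400; it does not say that 400 people will be scanned. The neuroimaging outcomes appear in a separate sentence about methods. What remains is that Project 3 lists imaging among its analyses and supplies only a figure for N=400.

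Two stronger readings should be set aside:
- A reader might infer that Project 2's r=0.2 contradicts Project 3. It does not: the two figures refer to different sample sizes, 200 and 400.
- A reader might infer that Project 2's companion figure, Cohen's d of 0.2, is also wrong. It holds at 80.4% power for a one-sample or within-person contrast with n=200. That suits a single cohort and the within-person task conditions in the Figure 2 legend (for example 2-back and 0-back). The article plans no comparison of two imaging groups against which the figure would fail.

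**Conclusion.** The stated detectable correlations for N=400 are wrong under either sidedness. Two-sided, they are too small by about 0.03 at 80% power (0.140 − 0.11) and 0.04 at 95% (0.179 − 0.14). The chance of missing a true r of 0.11 is about 40% rather than 20%, and of missing 0.14 about 20% rather than 5%; one-sided, these chances are about 29% and 12%. The stated pairs would both fit a two-sided test with roughly 650 subjects, but the article does not show where the error arose.

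For the imaging outcomes, the relevant two-sided values are about 0.20 and 0.25, on the article's expectation of about 200 participants with MRI.

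These results assume complete data, no covariate losses and no multiplicity adjustment, so they are best cases. As an illustration only, an assumed Bonferroni split over the three EF domains would raise the two-sided 80% value at N=400 to about 0.161. Missing blood samples would reduce the numbers for both objectives. The point is confined to the accuracy of stated figures; it does not show that 400 is an inadequate sample for the EF objective.

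**What to change.** Replace the power sentence in Project 3, Proposed analysis, with wording such as: *N=400 gives 80% power for r=0.14 and 95% power for r=0.18 (two-sided alpha 0.05); for the imaging objective, n of about 200 gives 80% power for r=0.20 and 95% power for r=0.25.* If a one-sided test is intended, say so and give 0.124 and 0.164 for N=400, with 0.175 and 0.230 for n=200.

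The cost is one sentence. No participants are added and no analysis changes; the stated sensitivity simply becomes less favourable.
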